## Protocol

### Objectives and outcome measures

**
Overarching aim
**

To establish the safety and feasibility of an established BCG controlled human infection model in Liverpool, UK.

**
Specific objectives (
Table 1)
**

1.   Confirm microbiological and molecular recovery of BCG at the intradermal injection site by gold standard skin punch biopsy (punch biopsy) 14 days after challenge

2.   Confirm safety and tolerability in healthy adult participants

3.   Determine agreement between less invasive skin biopsy techniques (including swabs, skin scrapes and microbiopsy) compared to gold standard punch biopsy on microbiological and molecular recovery of BCG with an aim to employ less invasive methods within a refined protocol in future.

4.   Confirm optimal procedures to assess immune response to BCG intradermal challenge locally (skin tissue), systemically (blood) and in the respiratory mucosa (nasal samples).

**Table 1. T1:** Outcome measures: Objectives and endpoints.

	Objectives	Endpoints
**Primary**	To quantify BCG recovered from the intradermal BCG challenge site 14 days after injection	Culture and PCR quantification of BCG at intradermal challenge site by punch biopsy
**Secondary**	Confirm safety and tolerability of study procedures in participants	Actively (solicited) and passively collected data on adverse events
	Confirm agreement between BCG recovery between punch biopsy and minimally invasive skin biopsy	Pairwise comparison between culture and PCR quantification by punch and micro skin biopsy
	Confirm agreement between BCG recovery between punch biopsy and minimally invasive skin scrape	Pairwise comparison between culture and PCR quantification by punch biopsy and skin scrape
	Longitudinal quantification of BCG recovery from the intradermal BCG challenge site at 2, 7, 14, 21 and 28 days	Culture and PCR quantification of BCG at intradermal challenge site by non-invasive skin swab.
	Confirm laboratory assays for immune response to BCG at intradermal injection site	Skin biopsy cell pellet(s) examined for immune cell differentiation and antigen stimulation
	Confirm laboratory assays for immune response to BCG in systemic circulation	Immune cell activation and functional assays; and cytokine levels in blood
	Measure immune response to BCG injection in respiratory mucosa	Nasal scrape pellet and nasal lining fluid examined for cell differentiation and activation and cytokine expression

**
Study hypotheses
**

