### Study design

Prospective longitudinal controlled human infection study after intradermal injection with BCG SSI in two phases: Phase A is designed to confirm microbiological recovery and determine agreement between the current gold standard of skin punch biopsy 14 days after injection with minimally invasive biopsy techniques. Phase B is designed to refine and optimise immunological assays to measure local (using optimal minimally invasive techniques), systemic (blood) and respiratory mucosal responses to intradermal BCG injection.

**
Phase A
**

Ten participants will receive a single intradermal injection to the upper arm of BCG SSI 6–24 × 10
^5^ colony forming units in line with an optimised and established existing protocol
^
15
^. The BCG SSI strain has been chosen as the UK licensed vaccine for TB. The dose (3x higher than that used in routine vaccination) has been chosen based on study findings by Minhinnick
*et al.*
^
15
^, who demonstrated good mycobacterial recovery at this concentration with no increase in participant adverse events between the doses. Participants will be followed up longitudinally with active assessment for tolerability; adverse events; and serious adverse events. We will determine BCG SSI recovery from the intradermal injection site 14 days later by classical microbiology and molecular diagnostic techniques using gold standard punch biopsy
^
15
^ as our primary outcome measure. In parallel, and after local anaesthetic injection, we will obtain paired minimally invasive samples (skin swab, skin scrape
^
18
^ and microbiopsy
^
17
^ from the same skin site at 14 days and determine agreement of BCG SSI recovery by classical microbiology and molecular diagnostic techniques with punch biopsy

Parameters for progression from Phase A to Phase B are:

1.Participants able to tolerate study procedures2.No experimental challenge related SAE or SUSAR detected3.Confirmation of BCG recovery by classical microbiology or molecular techniques from punch biopsy at day 14 in all 10 participants who received intradermal BCG challenge4.Confirmation of BCG recovery by classical microbiology or molecular techniques from any of the minimally invasive skin sample technique (swab, scrape and microbiopsy) at day 14 in ≥9 participants who received intradermal BCG challenge.

**
Phase B
**

Twenty participants will receive a single intradermal injection to the upper arm of BCG SSI 6–24 × 10

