**Skin swabs** will be rolled across the intradermal injection site at each subsequent study visit to determine if BCG can be accurately recovered and quantified using this technique. There are conflicting reports in the literature on this technique: Blazevic
*et al.*
^
21
^ demonstrated that paired classical and qPCR microbiological quantification techniques demonstrated significant kinetic association. However, another study was unable to culture BCG by swabbing of the injection site
^
13
^. In phase B this procedure will only be conducted if the injection site has ulcerated and there is concern about secondary infection.

8.   
**Nasosorption** will be obtained because we expect BCG to stimulate the respiratory mucosa. Sample strips are similar to blotting paper and developed by Hunts Development Ltd (UK). Strips collect concentrated nasal lining fluid before the nasal wash to measure inflammatory responses induced by infection that may be associated with increased colonisation density and acquisition. Concentrated nasal fluid will be used to measure cytokine levels by multiplex bead array. Blotting paper will be held inside the nostril for up to 3 minutes until soaked. These will then be removed and placed in a microcentrifuge tube for storage.

9.   
**Nasal wash will be obtained in a subset of participants only.** This will be performed using a modified Naclerio method. This is a well-used and validated technique to collect nasal bacterial specimens with which we now have 4 years’ experience. Briefly, 5ml of saline is instilled and held for a few seconds in the nares before being allowed to drip in to a sterile Galli pot; this is usually repeated up to 20ml in total. In the event of NW loss (defined as cough/sneeze/swallow) the procedure may then be repeated to obtain an adequate specimen.

10.   
**Nasal cells** will be collected after nasal wash using a nanosampling method in which cells are obtained through minimally invasive superficial nasal scrape biopsies (rhinoprobe) and participants can be biopsied multiple times with no significant side effects. Up to 4 samples will be obtained at each nasal sampling visit. If no cells are visible on the rhinoprobe following sampling, the sample can be repeated immediately.

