**Serious Adverse** **Event (SAE)**	A serious adverse event is any untoward medical occurrence that: • Results in death • Is life-threatening • Requires inpatient hospitalisation or prolongation of existing hospitalisation • Results in persistent or significant disability/incapacity • Consists of a congenital anomaly or birth defect Other ‘important medical events’ may also be considered serious if they jeopardise the participant or require an intervention to prevent one of the above consequences. NOTE: The term "life-threatening" in the definition of "serious" refers to an event in which the participant was at risk of death at the time of the event; it does not refer to an event which hypothetically might have caused death if it were more severe.
**Serious Adverse** **Reaction (SAR)**	An adverse event that is both serious and, in the opinion of the reporting Investigator, believed with reasonable probability to be due to one of the trial treatments/challenge agents, based on the information provided.
**Suspected** **Unexpected** **Serious Adverse** **Reactions (SUSAR)**	A serious adverse reaction, the nature and severity of which is not consistent with the information about the challenge agent.

**
Adverse events
**

Table 5 details the expected adverse events of BCG injection and challenge site biopsy

**
Adverse event severity assessment
**

Unexpected adverse events will be recorded and these AEs will be graded by severity as follows (where 0 = absent, 1 = mild, 2 = moderate, 3 = severe).
Table 6 details this process:

**
Causality assessment
**

The relationship of each adverse event to inoculation must be determined by a medically qualified individual within the study team according to the following definitions:

0 = No relationship:

•   No temporal relationship to BCG intradermal injection

•   Definite alternative aetiology (clinical, environmental or other intervention), and

•   Does not follow pattern of recognised response to BCG intradermal injection;.

1 = Unlikely relationship:

•   Unlikely temporal relationship to BCG intradermal injection or;

•   Alternate aetiology likely (clinical, environmental or other intervention), and

•   Does not follow pattern of recognised response to BCG intradermal injection

2= Likely relationship:

•   Reasonable temporal relationship to BCG intradermal injection, and

•   Event not readily explained by alternative aetiology (clinical, environmental or other interventions), and

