•   Similar pattern of response to that seen to BCG intradermal injection, or

3 = Definite

•   Reasonable temporal relationship to BCG intradermal injection and

•   Event not readily produced by alternative aetiology (clinical, environment, or other interventions), and

•   Known pattern of response to BCG intradermal injection.

The chief investigator (CI), with the consultation of the trial steering committee (TSC), if required, will determine causality of AEs. The greatest degree of causal relationship (definite > probable > possible > unlikely related > not related) determined by either the PI or TSC after their discussions will determine the ultimate classification of the AE. Definite (4), probable (3) and possible (2) are considered to be related. No relationship (0) and unlikely (1) are unrelated.

**Table 5. T5:** Expected adverse events.

Expected adverse events
Pain/tenderness at the injection or biopsy site
Redness at the injection or biopsy site
Swelling at the injection or biopsy site
Warmth at the injection or biopsy site
Scaling/pustules at the injection or biopsy site
Transient ipsilateral axillary lymphadenopathy <1cm diameter
Scar at challenge (and biopsy site)
Headache
Fever (>38.3°C)

**
Procedure for recording adverse events
**

Participants will be asked to complete diary cards for 14 days after BCG challenge. They will be provided with a thermometer and tape measure to enable daily recording of temperature and local reactions at the injection site.

The diary cards will be reviewed at follow up visits and adverse events recorded in the CRF. Outside the diary card periods, expected local and systemic AEs (listed in
Table 5) will be specifically asked about and graded by severity (as detailed in
Table 6). Participants will be given the opportunity to report any other new symptoms since the last visit with start and stop dates and any treatments undergone.

All AEs (whether reported by the volunteer or solicited by the Investigator) will be clinically assessed at each visit and recorded in the CRF.

The following information will be recorded: description, date of onset and end date, severity and any treatment or intervention undertaken. The severity of events will be assessed on the following scale: 1 = mild, 2 = moderate, 3 = severe.

An assessment of relatedness to the BCG challenge will then be made by the Investigator.

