### Risk assessment

A risk assessment and monitoring plan will be prepared before the study opens and will be reviewed as necessary over the course of the study to reflect significant changes to the protocol or outcomes of monitoring activities. Specific risks are outline below.

**
Phlebotomy
**

The total amount of blood collected over the study period will be a maximum of 350mL. This amount should not compromise otherwise healthy participants. Risks occasionally associated with venepuncture include pain and bruising at the site of venepuncture, light-headedness, and syncope (rarely).

**
Nasal, nasopharyngeal and throat samples
**

This may cause some discomfort, eye watering or a small spot of blood. Participants may swallow the saline during nasal wash which may taste salty.

**
Challenge with BCG SSI
**

Full details are given in the summary of product characteristics (SmPC). In brief:

**
*Local reaction from intradermal BCG injection*
**

•   An inflammatory reaction as manifested by redness and swelling is expected to occur at the site of injection, followed by a local lesion that may ulcerate to be moist for up to three weeks. This heals over some weeks to months to leave a small flat scar. It is also possible to develop some swelling (<1cm diameter) of axillary lymph nodes.

•   Uncommonly (less than 1 in 100 people) swelling of axillary lymph nodes to more than 1cm across, or an ulcer that discharges fluid at the injection site may occur.

•   Rare side effects (less than 1 in 1000 people) include inflammation of lymph nodes leading to abscesses and discharge of fluid from the swellings.

**
*Systemic reactions*
**

•   Systemic reactions to BCG are rare (less than 1 in 1000 people) and include low-grade fever and headache, and allergic reactions. Disseminated complications of BCG, such as bone infections, have also been reported, but are extremely rare and have usually been reported in immunocompromised, not immunocompetent, individuals.

**
*Allergic reactions*
**

•   Allergic reactions from mild to severe may occur in response to any constituent of a medicinal product. Anaphylaxis is extremely rare but can occur.

**
Skin biopsy
**

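### Tolerability of study procedures is a secondary objective, but the nasal-sampling and venepuncture effects that the protocol names have no named prompt and no attribution to the procedure

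*Protocol article*

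**What the plan says.** Table 1 of the protocol article gives as a secondary objective "Confirm safety and tolerability of study procedures in participants", with the endpoint "Actively (solicited) and passively collected data on adverse events". The first criterion for moving from Phase A to Phase B is also about procedures: "Participants able to tolerate study procedures".

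Under Safety reporting, the list of events is introduced with "Table 5 details the expected adverse events of BCG injection and challenge site biopsy". The paragraph on recording adverse events says that, outside the diary periods, staff ask specifically about the "expected local and systemic AEs (listed in" Table 5). During the 14 days after challenge, participants keep a diary in which they grade whatever symptoms they have. The only measurements named for that diary are temperature and reactions at the injection site. At visits, participants may also mention anything new since the last visit. Table 6 has an Other AEs row for grading.

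The Risk assessment section describes the effects of the remaining procedures. For nasal, nasopharyngeal and throat samples: "This may cause some discomfort, eye watering or a small spot of blood". For phlebotomy: "Risks occasionally associated with venepuncture include pain and bruising at the site of venepuncture, light-headedness, and syncope (rarely"). Relatedness of every event is assessed against the BCG injection.

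**The concern.** The objective is about procedures, while the named prompts and the causality scale are about the BCG injection and the skin biopsy. Events that are prompted by name tend to be recorded more completely than events left to an open question. So the record for nasal sampling and venepuncture may be thinner than the record for the skin procedures because of how it was collected.

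Attribution is the second gap. Even when a nosebleed or a faint is recorded, no field is described that links it to the procedure that caused it, so a tolerability result per procedure cannot be read directly from the data. The protocol says of nasal cell collection that "participants can be biopsied multiple times with no significant side effects". Unprompted collection in Phase B would be weak evidence for or against that description.

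**Working it through.** No figure in the plan bears on this point, so the check sets the sections side by side and counts visits.

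**1. Named effects against the named list.**

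| Procedure | Effects named under Risk assessment | In Table 5? |
|---|---|---|
| BCG injection | Local reaction, axillary node swelling, fever, headache | Largely yes |
| Skin biopsy | Scar; local infection | Scar yes; local signs at the biopsy site yes |
| Nasal and throat sampling | Discomfort, watering eyes, slight bleeding | No |
| Venepuncture | Pain, bruising, light-headedness, syncope | No |

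The nasal scrape is itself described as a biopsy in the clinical samples section. The Table 5 rows on the biopsy site still do not reach it, because the introducing sentence ties them to the challenge site.

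**2. Timing.** By the nominal days of Table 2, nasosorption and nasal scrape in Phase B fall on six visits; nasal wash has the same schedule in a subset.

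| Day | Nasal sampling (Phase B) | Diary running | Prompts described |
|---|---|---|---|
| 0, 2, 7 | Yes | Yes | Open diary, open question |
| 14 | Yes | Last nominal day | Open diary, open question |
| 21, 28 | Yes | No | Table 5 list, open question |

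Four of six nasal visits lie in the diary period and two lie outside it. Day 28 is also the last scheduled visit. The open question looks back to the previous visit, so nothing scheduled asks about effects that follow the day 28 sampling.

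For venepuncture, Table 2 shows blood up to day 14. Table 7 marks blood at all seven visits, and the 350 mL maximum equals 7 × 50 mL. The gap on days 21 and 28 is therefore certain for nasal sampling and depends on the table read for venepuncture.

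**3. Volume.** With up to 4 nasal samples per visit:

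- Scrapes: 4 × 6 = 24 per person, and 24 × 20 = 480 in Phase B at most.
- Of these, after the diary ends: 4 × 2 = 8 per person, and 8 × 20 = 160.
- Nasosorptions: 6 × 20 = 120, of which 2 × 20 = 40 come after the diary ends.

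**4. Attribution.** The causality scale runs from no relationship to definite, each level worded in terms of the intradermal injection. Its lower levels list another intervention as an alternative cause. A nosebleed straight after a nasal scrape would score 0 or 1 and be classed as unrelated. That is correct with respect to BCG, but it leaves no positive statement that the scrape caused it.

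**5. What Phase B could show at best.** If no nasal event were recorded in 20 people and capture were complete, the upper limit of the two-sided 95% interval for the per-person rate would be 1 − 0.025^(1/20) = 0.168, about 17%. Incomplete capture makes that limit optimistic, but the documents give nothing from which to say by how much.

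**The case against.** The strongest reply is that open-ended capture is already broad. Table 5 prompting is stated only for the time outside the diary, and the diary is not restricted to Table 5. Table 2 schedules adverse-event screening at every visit from day 0 to day 28. All events, volunteered or solicited, are assessed and recorded, and the Other AEs row can grade them. Watering eyes, a spot of blood or syncope would often happen in front of staff. The diary card's item list is not shown, and an article may fairly leave it to the full protocol. The endpoint expressly includes passively collected data. All of this stands. A reader might infer that active solicitation is confined to Table 5, or that no solicited tolerability data will exist for these procedures; the documents support neither.

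Three further inferences fail:

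- That the Phase A decision is undermined. In Table 2, nasosorption, wash and scrape occur only in Phase B, so their ascertainment cannot affect that decision.
- That a comparison of nasal with skin procedures will be biased, or that the transfer to Malawi depends on the nasal data. No such comparison is planned, and the Discussion speaks of transferring procedures in general.
- That the 17% limit can be scaled up by an assumed reporting fraction. The documents give none, and a per-event fraction cannot be applied to a per-person rate. For illustration only, if an event recurred at all six visits and each had an independent 30% chance of being reported, at least one report would arise with probability 1 − 0.7^6 = 0.88.

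The reply does not meet two things: the absence of any described prompt by name for effects the protocol itself lists, most clearly on days 21 and 28, and the absence of attribution to the procedure. The DSMC paragraph mentions relatedness to study procedures, but only for SAEs and AESIs and only to say that review does not depend on it.

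**Conclusion.** The point holds as a minor, inexpensive improvement to one secondary endpoint; the primary outcome is not affected. The stated objective is wider than the named prompts and the causality scale that serve it. Nasal and venepuncture effects can be captured, but through open reporting and staff observation, and without a described link to the procedure. Tolerability of nasal sampling may therefore be under-ascertained in Phase B, where this study's evidence on nasosorption, wash and scrape arises. The exposed part is two of six nasal visits for prompting, and all six for attribution.

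This assumes that the diary card does not already name these events and that the eCRF has no field for relatedness to each procedure. If the card does name them, the prompting gap shrinks to the period from day 14 onward, and the attribution gap remains.

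**What to change.** - Add the nasal-sampling and venepuncture effects already listed under Risk assessment to the solicited events. A separate block beside Table 5, arranged by procedure, would leave the SmPC-based judgement of expectedness for BCG untouched.
- Ask about them at each sampling visit, both for effects since the last visit and before the participant leaves. The second question matters most on day 28, which has no later scheduled visit.
- Grade them with the Other AEs row of Table 6.
- Record relatedness to the specific procedure as well as to the BCG injection.
- Tabulate events by procedure, with the number of participants and of procedures as denominators.

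The cost is a few extra eCRF fields per visit, with no new visit or sample. The downside is that more mild events will be recorded, which the tabulation by procedure makes easy to interpret.

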AEs considered related to the BCG challenge as judged by a medically qualified investigator or the Sponsor will be followed either until resolution, or the event is considered stable.

**Table 6. T6:** Grading of adverse events.

Adverse Event	Grade	Measurement
Pain/tenderness at the injection or biopsy site	0 1 2 3	No pain at all Painful on touch, easily tolerated Painful when limb is moved, interferes with daily activity Severe pain at rest, interferes with daily activity
Redness at the injection or biopsy site	0 1 2 3	0mm 1–50mm 51–100mm >100mm
Swelling at the injection or biopsy site	0 1 2 3	0mm 1–20mm 21–50mm >50mm
Fever (oral)	0 1 2 3	≤37.5°C 37.6 – 38.0°C 38.1 – 38.9°C ≥39.0°C
Other AEs	0 1 2 3	Absence of symptom Awareness of symptom but tolerated; transient or mild discomfort; little or no medical intervention required Mild to moderate discomfort leading to interference with usual activity, some minimal medical intervention/therapy may be required. Significant interference with daily activity; some assistance usually required; medical intervention/therapy required; hospitalisation possible

**
Reporting procedures for Serious Adverse Events (SAEs) and Suspected Unexpected Serious Adverse Reactions (SUSARs)
**

Any serious adverse event considered by the CI to be related to the challenge agent and unexpected will be reported to the REC. As the challenge agents are vaccines with Marketing Authorisation, the mechanism for reporting any SAEs to the MHRA is via yellow card.

**
Follow up and outcome of adverse events
**

Those adverse events which are unexpected and likely to be related to the BCG, whether serious or not, which persist at the end of the study will be followed up by the Investigator until their resolution. Additional follow-up visits may be arranged to enable this. As appropriate, participants with ongoing AEs may be advised to consult their General Practitioner (National Health Service) or the study team will arrange specialist review within the NHS. The outcome of all related non-serious AEs and any SAEs will be assessed as:

Recovered/resolvedRecovered with sequelae/resolved with sequelaeUnknownOngoing at end of studyFatal

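### Adverse-event causality is scored only against the BCG injection, so harm from biopsies and other sampling cannot be attributed properly, although safety of the study procedures is a stated objective

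*Protocol article*

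**What the plan says.** Table 1 (Objectives and outcome measures) gives the secondary safety objective as "Confirm safety and tolerability of study procedures in participants". Its endpoint is solicited and passively collected adverse-event data, with no filter on cause.

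The causality instrument is under Safety reporting, Causality assessment: "The relationship of each adverse event to inoculation must be determined by a medically qualified individual within the study team". Its four codes are all defined by timing and pattern relative to the BCG intradermal injection. Other interventions appear as follows:

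- Code 0: "Definite alternative aetiology (clinical, environmental or other intervention), and" an event that does not look like a recognised BCG response.
- Code 1: "Alternate aetiology likely (clinical, environmental or other intervention), and" the same condition on pattern.
- Code 2: "Event not readily explained by alternative aetiology (clinical, environmental or other interventions), and" a pattern similar to that of BCG. Code 3 has an equivalent exclusion.

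Codes 0 and 1 are then declared unrelated. The subsection on recording adverse events repeats that relatedness means relatedness to the BCG challenge.

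Several rules use that classification:

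- Follow-up: "AEs considered related to the BCG challenge as judged by a medically qualified investigator or the Sponsor will be followed" to resolution or stability.
- Ethics-committee reporting: "Any serious adverse event considered by the CI to be related to the challenge agent and unexpected will be reported to the REC".
- Progression from Phase A to Phase B, criterion 2 (Study design): "No experimental challenge related SAE or SUSAR detected".
- Outcome: assessed for related non-serious events and for any SAE.

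**The concern.** The protocol sets out to show that its procedures are safe, and it foresees harm from them. Table 5 covers biopsy-site events, Table 6 grades them, and the Risk assessment names biopsy-site infection and allergy to local anaesthetic. The scale that assigns cause has no place for those harms except as evidence against a BCG relationship. An investigator who follows the instructions exactly would label a clear procedure harm as unrelated, and the rules that depend on that label would not apply to it. At stake are the attribution of harm in the safety report and the reach of the follow-up, outcome, reporting and progression rules.

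**Working it through.** No figure in the plan is at issue, so the check is a classification exercise on the text, followed by a count of exposures.

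**Step 1. Apply the scale to three kinds of event.**

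- *Reaction to local anaesthetic at the day 14 visit.* The other intervention is the evident cause, and an immediate reaction to an injection given two weeks after BCG does not follow the BCG pattern. Codes 2 and 3 are ruled out because another intervention readily explains the event. Code 0 applies if no temporal link to BCG is accepted. Otherwise code 1 applies, because its timing and alternative-cause conditions are joined by 'or'. Either code means unrelated.
- *Nosebleed after nasal scraping (Phase B).* The same reasoning gives code 0 or 1, hence unrelated.
- *Redness, swelling or pustules after a biopsy taken at the injection site.* Table 5 lists these for both the injection and the biopsy. Codes 0 and 1 require that the event does not look like a BCG response, and this one does. Codes 2 and 3 require that no other intervention readily explains it, and the biopsy does. No code fits. A discharging wound infection may also fall here, because the Risk assessment lists a discharging ulcer as a recognised, uncommon BCG reaction.

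The codes are defined as 0 to 3 but later used as 0 to 4. That is a separate inconsistency. It does not affect this result, because 0 and 1 are stated to be unrelated either way.

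**Step 2. Trace what depends on the label.**

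| Rule | Relatedness it uses | Reaches a procedure harm coded 0 or 1? |
|---|---|---|
| Recording and grading of AEs | none | yes |
| Follow-up to resolution or stability | BCG challenge | no |
| Follow-up of unexpected events persisting at end of study | BCG | no |
| Outcome, non-serious events | related | no |
| Outcome, SAEs | none | yes |
| Ethics-committee reporting of SAEs | challenge agent | no |
| Progression criterion 1 | none (tolerance of procedures) | yes, no threshold stated |
| Progression criterion 2 | experimental challenge | no |
| DSMC review | none (SAEs and AESIs) | SAEs yes; non-serious only if an AESI, defined as specific to the challenge agent |

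The DSMC section speaks of relatedness to study procedures, but the article defines no assessment of that relatedness.

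**Step 3. Count exposures per Phase B participant** (Table 2 and the list of clinical samples).

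- BCG injections: 1, with a causality scale.
- Microbiopsies: 2 per time point × 4 time points (days 0, 2, 7, 14) = 8.
- Nasal scrape samples: up to 4 per visit × 6 visits (days 0, 2, 7, 14, 21, 28) = up to 24.
- In addition: the punch biopsy with local anaesthetic scheduled in Table 2, nasosorption and venepunctures.

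These are procedures, not expected events. They show how much of the exposure lies outside the scale, not how many events would be mislabelled.

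**The case against.** The case on the other side has several strong parts.

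- *The endpoint is not filtered by cause.* All AEs are assessed at each visit and recorded with description, dates, severity and treatment. A reader might infer that procedure harms disappear from the safety endpoint. The documents do not support that: the events are kept, and only their attribution is missing.
- *Procedures are covered elsewhere.* Criterion 1 asks whether participants tolerate them. The DSMC reviews all SAEs and can advise that the trial be changed or not continue. A reader might infer that a serious biopsy complication would pass unexamined into Phase B. It would not, although it would not breach criterion 2 as worded.
- *Not every biopsy event is pushed to code 0 or 1.* This is correct for events that resemble a BCG reaction. They are left without a code, which is a different fault in the same scale.
- *No safety comparison between techniques is planned.* A reader might infer that such a comparison is spoiled. The planned comparisons concern BCG recovery. In Phase A the skin samples are also taken from one site at one visit, so attribution to a single technique would often be unreliable whatever field is added.
- *Ongoing events are not abandoned.* Participants may be advised to see their GP, or specialist review may be arranged, and antibiotics are foreseen for biopsy-site infection. These provisions stand, but they are not attribution or outcome rules.
- *The article is condensed.* The eCRF may hold a field for procedure relatedness. That cannot be seen. However, the article does not merely omit the point: it states twice that relatedness is to the inoculation or BCG challenge, and it writes its follow-up and reporting rules on that basis.

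These arguments narrow the consequences. They do not remove the mismatch between the scale and the objective.

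**Conclusion.** The concern holds in limited form. The scale as written classes clear procedure harm as unrelated when it does not resemble a BCG reaction, and leaves injection-site biopsy events that do resemble one without a fitting code. This conflicts with the secondary objective on study procedures and with the protocol's own list of expected biopsy-site events. The loss is attribution to procedures, together with the four sets of rules tied to BCG or challenge relatedness: follow-up, outcome of related non-serious events, ethics-committee reporting and progression criterion 2.

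The objective is secondary and descriptive, in 10 + 20 = 30 participants, and no estimate or test changes. The conclusion assumes that 'other intervention' includes study procedures, which is its plain meaning and is nowhere excluded, and that no separate procedure-relatedness assessment exists in documents not shown. Because recruitment had not begun when the article was submitted, and the remedy is small, the correction is worth making.

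**What to change.** Record a second relatedness judgement for every AE, to a study procedure, beside the existing one to BCG. Name the procedure where it can be identified (for example punch biopsy, local anaesthetic, nasal sampling, phlebotomy). Group skin sampling as one category where several techniques are used at the same site and visit. Report AEs by relatedness to BCG and by relatedness to procedures.

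Then reconcile the progression parameters in Study design, the causality, recording, reporting and follow-up text in Safety reporting, and the DSMC section, so that each rule states which relatedness it uses. Which judgement should drive follow-up, reporting or progression is for the sponsor and investigators to decide; the need here is that the text says so. The mismatch between codes 0 to 3 and 0 to 4 can be corrected in the same edit.

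Cost: one eCRF field and wording changes, with no extra visit or sample. The reported number of related events may rise.
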